**4. STUDY POPULATION**

**4.1. Inclusion Criteria**

Each potential subject must satisfy all of the following criteria to be enrolled in the study.

- Signed informed consent
- Age >18
- Patient suitable for 68Ga-PSMA PET/CT re-staging according to clinical practice (Previous radical prostatectomy with histological result of Prostate adenocarcinoma +/-postoperative prostate bed radiotherapy (adjuvant or salvage setting), with a biochemical relapse defined as a PSA > 0.2 and <1

1. **Exclusion Criteria**

- ADT administration within 6 months from studyenrollment
- Persistent elevation of PSA after RP measured within 16 weeks from surgery (> 0.1 ng/ml)

**5. STUDY PROCEDURES**

Patients will be observed after management in order to record clinical outcomes and explore prognostic factors in this cohort. According to clinical practice, the following guideline will be adopted for prostate bed RT and SBRT on all sites of disease (pelvic nodal or oligometastatic)

*1: Prostate bed RT*

Postoperative RT to prostate bed will be administered in case of negative PET PSMA findings or positive findings within prostate bed. Clinical Target Volume (CTV) will be defined according to EORTC guidelines [Poortmans 2007], a CTV to Planning Target Volume (PTV) margin of 5-8 mm will be added according to clinical practice and Image guidance protocols adopted. Both 3D conformal or Intensity modulated RT /Volumetric Modulated Arc Therapy (3D CRT or IMRT/VMAT) are allowed, provided that at least 66 Gy in 33 fractions, or equivalent dose/fractionation schedules, are delivered. Dose intensification (e.g 72-74 Gy in 36-37 fractions or equivalent dose/fractionation schedules) will be provided in case of positive PSMA/PET-CT findings inside prostate bed. At least 95% of PTV should be covered by 95% prescription isodose. Less than 10% of the PTV should be higher than the 105% prescription isodose. Dose constraints to Organs at risk (OAR) should respect QUantitative Analysis of Normal Tissue Effects in the Clinic (QUANTEC) report [Marks 2010]. In case of positive findings within prostate bed in patients who did not received postoperative prostate bed RT, Stereotactic Salvage RT (e.g. 35 Gy in 5 fractions on macroscopic recurrence) is allowed within site-specific study protocols.

*2: SBRT on all sites of disease (pelvic nodal or oligometastatic)*

The GTV will be any demonstrable abdominal nodal or bone metastatic disease detected by PSMA PET/CT. Morphological, topographical and metabolic informations should be integrated to delineate the target volumes. Rigid or deformable co-registration is allowed. No CTV is allowed for SBRT treatments. A GTV to PTV margin of 3-5 mm will be added according to clinical practice and image guidance protocols adopted.

The following dose/fractionation schedules could be adopted to perform SBRT:

| Total dose (Gy) | Dose per fraction (Gy) | Number of fractions |
| --- | --- | --- |
| 24 | 8 | 3 |
| 27 | 9 | 3 |
| 30 | 10 | 3 |
| 36 | 12 | 3 |
| 30 | 6 | 5 |
| 35 | 7 | 5 |
| 40 | 8 | 5 |
| 45 | 9 | 5 |
| 36 | 6 | 6 |
| 45 | 7.5 | 6 |

Dose constraints to Organs at risk (OAR) should respect report of AAPM Task group 101 [Benedict 2010]. A Simultaneous Integrated Protection (SIP) protocol could be adopted to preserve critical OAR.

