**2. OVERVIEW OF STUDY DESIGN**

**2.1. Hypothesis:**

This observational study was designed to evaluate PFS after PSMA-PET/CT based salvage approach for patients affected by BR after RP.

- 1. **Study design**

This is a prospective observational multicenter study including patients treated with upfront RP +/- postoperative prostate bed radiotherapy, with histological result of Prostate adenocarcinoma, affected by BR (defined as PSA > 0.2 ng/ml) with a PSA at recurrence < 1 ng/ml. Patients will be staged with centralized 68Ga-PSMA PET/CT and treated with a pre-defined approach based on 68Ga-PSMA PET/CT findings, according to routine clinical practice:

| Negative 68Ga-PSMA PET/CT or positive findings within prostate bed | Prostate bed RT*, **, *** |
| --- | --- |
| 68Ga-PSMA PET/CT detecting pelvic nodal recurrence (defined as nodal disease < 2 cm under aortic bifurcation) amenable with stereotactic body radiation therapy (SBRT) on all sites of disease | SBRT to positive nodal disease |
| Abdominal nodal or bone oligometastatic disease (defined as < 3 non visceral lesions, according to Association of Radiotherapy and Clinical Oncology (AIRO) definition [D’angelillo 2019]) amenable with stereotactic body radiation therapy (SBRT) on all sites of disease | SBRT on all sites of disease |
| Abdominal nodal or bone metastatic disease (> 3 lesions or non-amenable with SBRT) and/or visceral disease. | ADT+/-other systemic therapies available for metastatic hormone sensitive pCa at physician discretion |

**For patients who did not previously received prostate bed RT, dose intensification (e.g 72-74 Gy in 36-37 fractions or equivalent dose/fractionation schedules) will be provided* *in case of positive PSMA/PET-CT findings inside prostate bed. In this case, Stereotactic Salvage RT (e.g. 35 Gy in 5 fractions on macroscopic recurrence) is allowed within site-specific study protocols.*

*** For patients who already received prostate bed RT in postoperative setting with negative findings within prostate bed, observation and PSMA-PET/CT re-staging at further PSA progression (defined as > 25% PSA increase if compared to PSA at recurrence) will be performed*

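### Section 5 directs prostate bed RT and dose intensification without the prior-RT limits set in the Section 2 footnotes (minor inconsistency)

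*Protocol*

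**What the plan says.** Section 2 (Study design) says that patients are "treated with a pre-defined approach based on 68Ga-PSMA PET/CT findings" and sets this out in a table. The first row gives prostate bed RT for a negative scan or for uptake in the bed, and carries three footnotes:

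- The first limits intensification to men whose bed has not been irradiated: "For patients who did not previously received prostate bed RT, dose intensification" applies when the bed is PET-positive. Stereotactic salvage RT is allowed as an alternative within site-specific protocols.
- The second covers men with earlier bed RT and a negative bed. They are observed, and the scan is repeated once PSA has risen more than 25% above its value at recurrence.
- The third covers men with earlier bed RT and a positive bed. The clinician may observe and re-stage later, or retreat the bed, for example with SBRT to 30 Gy in 5 fractions.

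Section 4.1 admits men with earlier adjuvant or salvage bed RT, so the last two footnotes apply to patients the study means to enrol.

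Section 5 opens by saying that "the following guideline will be adopted for prostate bed RT and SBRT on all sites of disease". Item 1 then states the indication: "Postoperative RT to prostate bed will be administered in case of negative PET PSMA findings or positive findings within prostate bed". It allows 3D conformal or intensity-modulated techniques "provided that at least 66 Gy in 33 fractions, or equivalent dose/fractionation schedules, are delivered", and says that intensification (e.g. 72-74 Gy in 36-37 fractions or equivalent) "will be provided in case of positive PSMA/PET-CT findings inside prostate bed". Only the closing sentence of item 1 mentions earlier treatment: for a positive bed "in patients who did not received postoperative prostate bed RT, Stereotactic Salvage RT" is allowed.

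**The concern.** A treatment rule is stated twice, and the second statement drops a condition on which the first depends. Section 5 contains the dose and planning instructions, so staff at a site may well consult it on its own. Taken alone, its first sentence would send a previously irradiated man with a negative scan to a full course of bed RT, where Section 2 says to observe him. Its intensification sentence would send a previously irradiated man with a positive bed to an escalated course, where Section 2 leaves a choice between observation and a retreatment.

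What is at stake is mainly safety: Section 7 itself lists urethral stricture, cystitis, proctitis and incontinence as risks of the radiotherapy. There is also a smaller analytical cost. In a multicentre study of a pre-defined approach, two versions of the rule leave it unclear what counts as following that approach.

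**Working it through.** No figure in the plan is at issue, so the check sets the two sections side by side for each kind of patient in the first row of the table. The inputs are the Section 2 table and footnotes, Section 4.1 for eligibility, and Section 5, items 1 and 2.

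| Prior bed RT | PET result | Section 2 with footnotes | Section 5, item 1, read literally | Agree? |
| --- | --- | --- | --- | --- |
| No | Negative | Bed RT | Bed RT, at least 66 Gy in 33 fractions or equivalent | Yes |
| No | Bed-positive | Bed RT with intensification, or stereotactic RT within site-specific protocols | The same | Yes |
| Yes | Negative | Observation, later re-staging | Bed RT, at least 66 Gy in 33 fractions or equivalent | No |
| Yes | Bed-positive | Observation, or retreatment (e.g. 30 Gy in 5 fractions) | Bed RT with intensification, e.g. 72-74 Gy in 36-37 fractions or equivalent | No |

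The sections agree in 2 of 4 cases and differ in 2 of 4; both differences are among men with prior RT. The third line is limited to wholly negative scans: Section 5 does not send a man with a clear bed but positive nodes to bed RT.

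The two conflicts differ in kind. With a negative scan, one section says observe and the other says treat. With a positive bed, one leaves a choice and the other directs treatment, with a different example dose.

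Nominal doses overstate the second gap, because fraction sizes differ. The usual conversion to 2 Gy fractions is D × (d + α/β) / (2 + α/β), where D is total dose and d is dose per fraction. The protocol gives no α/β, so values of 3 and 1.5 are assumed to show a range:

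- α/β = 3: 30 × (6 + 3) / (2 + 3) = 54 Gy
- α/β = 1.5: 30 × (6 + 1.5) / (2 + 1.5) = 64.3 Gy

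The courses of 66 Gy in 33 fractions and 72-74 Gy in 36-37 fractions are already at 2 Gy per fraction and need no conversion. The example retreatment is therefore below 72 Gy by 72 − 54 = 18 Gy or by 72 − 64.3 = 7.7 Gy, depending on the assumption. The direction of the difference is the same at both values.

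Item 2 of Section 5 does not close the gap. It covers pelvic nodal and oligometastatic disease, and its target is defined accordingly: "The GTV will be any demonstrable abdominal nodal or bone metastatic disease detected by PSMA PET/CT". Its dose table happens to list 30 Gy in 5 fractions, but not for the prostate bed. Item 1 is thus the only Section 5 text on bed findings, and it has no provision for observation or retreatment.

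**The case against.** The strongest reply is that the protocol can be read as consistent. The footnotes are explicit and are attached to the very row that Section 5 repeats, so Section 5 merely restates the general entry. Section 5 is introduced as guidance on delivery; most of item 1 concerns volumes, margins, coverage and constraints, and the 66 Gy minimum is a condition on the permitted techniques, not an order to treat. The protocol also tends to use the word postoperative for the first course of bed RT and calls a second course retreatment. On that usage the first sentence of item 1 never reaches previously irradiated men, and all four cases are compatible. Finally, treatment follows routine practice and earlier treatments are recorded at baseline (Section 6.1), so a clinician would have to overlook both the table and the patient's history for harm to follow.

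Much of this stands. The footnotes most likely govern, a reader of both sections can resolve the conflict, and the practical risk is low. The 2-of-4 disagreement exists only when Section 5 is read literally.

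It does not remove the point. The first sentence of item 1 states when RT is given, which is an indication and not a technique. The protocol sets no order of precedence between sections and does not define postoperative. The closing sentence of item 1 spells out the restriction to men without earlier bed RT, so the authors thought it needed saying there, yet the two rules before it lack it. The intensification sentence does not use the word postoperative at all, while the matching footnote in Section 2 does carry the restriction.

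**Conclusion.** The point holds as a minor inconsistency. Section 5, item 1, omits a condition that Section 2 makes decisive, and taken literally it gives the wrong instruction in both cases with previous bed RT. The conclusion rests on the wording alone and assumes nothing about the dose of the earlier course or the share of previously irradiated men, neither of which the protocol gives. The number of patients affected is therefore unknown. That the footnotes are the intended rule is a reasonable inference, not something the protocol states. The target of 180 patients, the precision figures and the endpoint definitions are unaffected.

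**What to change.** Amend Section 5, item 1, in two places:

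1. Limit both the sentence giving the indication for bed RT and the sentence on dose intensification to patients without previous prostate bed RT.
2. Add one sentence: patients with previous prostate bed RT follow the footnotes to the Section 2 table.

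The sponsor's clinicians should first confirm that the footnotes are the intended rule. The cost is a short wording change in an amendment. Because earlier treatments are already collected at baseline under Section 6.1, it needs no new data, visits or patients.

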**6. STUDY EVALUATIONS**

**6.1 Pre­Treatment Evaluation**

Baseline evaluations include:

- - demographics data;
  - active co­morbidities and current medical treatments;
  - Pathological staging, margin status, PSA value and Gleason Score at the time of prostate cancer diagnosis;
  - previous treatments for prostate cancer;
  - Baseline PSA at BR
  - Imaging procedures:
- Staging with PSMA PET/CT
  - assessment of Performance Status with the Eastern Cooperative Oncology Group (ECOG) Score;
  - Baseline Quality of life assessment measured by EORTC QLQ-C30 and EORTC QLQ-PR25 (baseline evaluation should be performed before radiotherapy beginning);
  - Blood samples to detect baseline expression of a specific panel of miRNA (miR-186, miR-26a, miR-374a, miR-410, miR-660)
  1. **Evaluation During Treatment**

Patients will be evaluated as follows:

- After initial PSMA PET/CT, treatment modalitywill be recorded to assess the proportion of management changes induced by positive PSMA PET/CT results
- every 3 months from therapy start with ECOG Score EORTC QLQ-C30 and EORTC QLQ-PR25
- PSA value every 3 months from therapy start
- PSMA PET/CT will be repeated in case of biochemical progression, defined as a PSA increase above 0.2 ng/ml for patients with a PSA nadir < 0.2 ng/ml or 2 consecutive PSA increases >25% if compared to nadir in patients with a PSA nadir > 0.2 ng/ml is detected.

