**** For patients who already received prostate bed RT in postoperative setting with positive findings within prostate bed, both observation and PSMA-PET/CT re-staging at further PSA progression or prostate bed retreatment (e.g SBRT for a total dose of 30 Gy in 5 fractions) will be allowed according to clinician choice*

Planned size of the overall study population is 180 patients. Data about demographics, PSA, comorbidities and current drug therapies up to 45 days prior to enrollment will be collected at baseline. The study will consist in the observation of outcomes after 68Ga-PSMA PET/CT staging and following postoperative tailored management. Total planned duration of the study is 84 months, consisting in 36 months enrollment period and a later phase of 48 months in which patients will continue to be submitted to periodic checks every 3 months.

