**2.3. Study design rationale**

Standard approach for BR after RP is SRT [Thompson 2013]. However, emerging imaging modalities, such as 68Ga-PSMA PET/CT, allowed to effectively estimate location and actual burden of disease, and are currently used in clinical practice. A tailored approach based on 68Ga-PSMA PET/CT findings allows to increase clinical outcomes and reduce unnecessary toxicity (e.g prostate bed RT in patients with sublinical metastatic disease, undetectable with conventional staging). However, prospective data about this issue could help to accurately assess prognostic factors associated to clinical outcomes after a tailored postoperative approach.

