**3.3 Study endpoints**

*Primary endpoint*

Primary objective of the study will be to explore prognostic factors correlated with rate of 2 years PFS. PFS is defined as time from end of salvage treatment performed at first relapse to documented biochemical progression or radiological progression (or both), death from any cause or censoring at date of last follow-up. Biochemical progression is defined as the date in which a PSA increase above 0.2 ng/ml for patients with a PSA nadir < 0.2 ng/ml or 2 consecutive PSA increases >25% if compared to nadir in patients with a PSA nadir > 0.2 ng/ml is detected. Radiological progression will be defined as the occurrence of any new lesion detectable with PSMA PET/CT and/or any other molecular/radiological exam, which will be performed in case of biochemical or clinical progression

*Secondary endpoints*

- Explore prognostic factors correlated with Overall survival (defined as time between end of tailored treatment after 68Ga-PSMA PET/CT and death)

- Explore prognostic factors correlated with Cause specific survival, defined as time between end of tailored treatment and death for prostate Cancer

- Explore prognostic factors correlated with Radiological PFS, defined as the occurrence of any new lesion detectable with PSMA

PET/CT and/or any other molecular/radiological exam, which will be performed in case of biochemical or clinical progression

-Record rate of patients with impaired quality of life measured by EORTC QLQ-C30 and EORTC QLQ-PR25 at 2 years (defined as decrease by 10 points in global health scale and functional scales or increase by 10 points in symptoms scales compared with baseline, without later improvement superior by 10 points)

-To assess the proportion of management changes induced by positive PSMA PET/CT results

-To assess the association between PSMA PET/CT detection rate and baseline detection of a specific panel of miRNA (miR-186, miR-26a, miR-374a, miR-410, miR-660)

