**6.3 Statistical Analysis**

Considering the observational nature of the present protocol, a strict criterion for a target accrual would not be needed. However considering a reported rate for 2 year progression free survival after salvage radiotherapy alone of 80% [Carrie 2019], a sample size of 172 patients would be needed to estimate with a 6% precision margin and a 95% confidence interval. Considering a 5% drop out rate, 180 patient are the target accrual fixed for this study. In case this target could not be achieved, smaller sample size would lead to 95% confidence intervals ranging 73-86% (for N=150), 72-87% (for N=120), and 70-88% (for N=90), i.e. with a precision margin still within 10% (always assuming a 2-y PFS equal to 80%). Furthermore, considering that PSMA PET/CT has been shown to change therapeutic management in 34% of cases [DeAndreis 2020], 90 patients would be sufficient to assess with a 11% precision margins the rate of patients in whom re-staging allowed to tailor management. Considering the explorative nature of the translational objectives of the study, a target sample size will not be needed.

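### The management-change endpoint records treatment after the PET/CT but neither a pre-scan plan nor a reference treatment, so it shows departure from an assumed standard, not change induced by the scan

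*Protocol*

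**What the plan says.** Sections 3.2 and 3.3 of the protocol list this as a secondary objective and endpoint: "To assess the proportion of management changes induced by positive PSMA PET/CT results". The section on evaluation during treatment, which follows 6.1, supplies the data for it: "After initial PSMA PET/CT, treatment modalitywill be recorded to assess the proportion of management changes induced by positive PSMA PET/CT results".

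The protocol has two lists of baseline data. The study design section says: "Data about demographics, PSA, comorbidities and current drug therapies up to 45 days prior to enrollment will be collected at baseline". Section 6.1 adds pathology, PSA, imaging, performance status, quality of life and miRNA. Its only entry on earlier or planned therapy is "previous treatments for prostate cancer". Neither list includes the treatment intended before the scan.

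After the scan, patients are "treated with a pre-defined approach based on 68Ga-PSMA PET/CT findings, according to routine clinical practice". Section 2.3 names a general standard, "Standard approach for BR after RP is SRT", but nothing designates it as the comparator for this endpoint. Section 4.1 also admits patients who have had "postoperative prostate bed radiotherapy (adjuvant or salvage setting").

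Section 6.3 bases the precision of the endpoint on the statement that "PSMA PET/CT has been shown to change therapeutic management in 34% of cases", and says that 90 patients would give an 11% margin.

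**The concern.** A change needs a before and an after, and the protocol collects only the after. Whether a scan altered a decision then depends on what someone later supposes the decision would have been.

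The gap differs by patient group:

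- **No prior bed radiotherapy.** Salvage bed radiotherapy can be supposed as the plan. But the protocol's table assigns treatment from the scan finding, so the resulting rate is close to the share of patients with disease outside the bed. It says little about clinicians' decisions.
- **Prior bed radiotherapy.** The protocol states no treatment that would be given without PET. Its footnotes describe only what follows the scan: observation if the bed is negative, and observation or retreatment at the clinician's choice if it is positive.
- **Positive bed finding, no prior bed radiotherapy.** The protocol provides for dose intensification and allows stereotactic salvage treatment. It does not say whether either counts as a management change, and a field for modality alone may not capture intensification.

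An SAP, which may exist but is not at hand, can define a reference. It cannot recover an intention that was never recorded, and an intention stated after the scan is read may be coloured by the result.

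**Working it through.** **1. The plan's own figure.** Inputs from Section 6.3: expected rate 34%, N = 90. A 95% level is assumed, as stated there for PFS.

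- Normal approximation: 1.96 × √(0.34 × 0.66 / 90) = 9.8 points.
- Exact (Clopper-Pearson) interval: 24.3% to 44.7%. The wider side is 44.7 − 34 = 10.7 points, which rounds to 11.

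The stated margin is reproduced. It covers sampling error only and presumes that each patient can be classified as changed or not. The figure of 90 is given as sufficient; target accrual is 180, where the normal-approximation margin is 1.96 × √(0.34 × 0.66 / 180) = 6.9 points.

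**2. What can be classified from the data collected.**

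| Group | Known after the scan | Known before the scan | Change status |
|---|---|---|---|
| No prior RT, treated outside the bed | Modality | Nothing; bed RT can be assumed | Countable as departure from an assumed standard |
| No prior RT, positive bed only | Bed RT, intensified or stereotactic | Nothing; bed RT can be assumed | Depends on an unstated rule about dose and technique |
| Prior RT, positive scan, SBRT to nodal or bone lesions | Modality | Nothing | Very likely a change, since Section 5 defines the target from the PET/CT |
| Prior RT, positive scan, observation, bed retreatment or ADT | Modality | Nothing; no reference stated | Not identifiable |
| Any patient, negative scan | Modality | Nothing | Outside the numerator as the endpoint is worded |

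**3. Bound on the affected share.** Let f be the share with prior radiotherapy and s the scan positivity among them. The protocol gives neither. With all scanned patients as denominator, the part of the rate that could be counted either way is at most f × s. The assumed ranges are f = 20-50% and s = 30-60%.

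| | s = 30% | s = 60% |
|---|---|---|
| f = 20% | 0.20 × 0.30 = 6 points | 0.20 × 0.60 = 12 points |
| f = 50% | 0.50 × 0.30 = 15 points | 0.50 × 0.60 = 30 points |

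This is the distance between counting none and all of these patients as changed. It is an extreme bound, because irradiated patients given SBRT to PET-detected lesions can mostly be classified.

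**4. Comparison with the margin.** The bound reaches 11 points at f = 0.11 / 0.30 = 37% if s = 30%, and at f = 0.11 / 0.60 = 18% if s = 60%. Set against the full width of the exact interval at N = 90 (44.7 − 24.3 = 20.4 points), it is larger only in the upper part of the assumed range; for example, at s = 60% it needs f above 0.204 / 0.60 = 34%. A larger sample narrows the interval but not this bound.

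The unclassified bed intensification in patients without prior radiotherapy comes on top and cannot be sized from the protocol.

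**The case against.** A reader might infer that the endpoint cannot be measured at all. The documents do not support that. Sections 1.1 and 2.3 present salvage bed radiotherapy as the usual treatment. Prior treatment and post-scan modality are both recorded, so departures to nodal or bone SBRT or to ADT can be counted in patients without prior bed radiotherapy. SBRT to a lesion defined on the PET/CT could hardly have been planned before it, whatever the treatment history. This part of the objection stands.

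A reader might also treat every previously irradiated patient as indeterminate, which would put 20-50 points in doubt under the assumed range. That is too much: the endpoint counts only changes after positive scans, so irradiated patients with a negative scan cannot enter the numerator.

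Nor can it be shown that the 34% benchmark mismatches the endpoint. Restricting the numerator to positive scans does not fix the denominator, and how the cited study counted changes after negative scans is not in the protocol. The restriction itself is worded consistently in 3.2, 3.3 and the section on evaluation during treatment, and is a permissible choice.

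Finally, a reference fixed by prior-radiotherapy status could be named later without knowledge of the scan. That is true and gives a usable fallback. It still yields departure from a reference, not a change from the plan the clinician held.

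**Conclusion.** The concern holds in limited form. As written, the protocol does not observe a patient-level change attributable to PET/CT, because it records no intended management before the scan and names no reference treatment. In patients without prior bed radiotherapy the result is interpretable as departure from an assumed standard. In irradiated patients with a positive scan managed by observation, bed retreatment or ADT, it is not identifiable. Whether changes of dose or technique within bed radiotherapy count is left open.

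The share open to doubt among irradiated patients is at most 6-30 points. This rests on assumed values for prior-radiotherapy share (20-50%) and positivity (30-60%), on all scanned patients as denominator, and on extreme counting; the low end lies within the stated 11-point margin. The sample size and the primary endpoint are not affected. The change is worth making because the missing information is cheap to collect before the scan and cannot be recovered reliably afterwards.

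**What to change.** - **Section 6.1:** add one CRF item, completed and dated before the index PET/CT is read, giving the management the investigator would choose without it.
- **Section 3.3 and the section on evaluation during treatment:** define change as actual management compared with this recorded plan. State whether a change of dose or technique within bed radiotherapy counts. Use all scanned patients as denominator.
- **Reporting:** give the rate by prior radiotherapy (yes/no), and show changes after negative scans separately, so that the endpoint as now worded stays visible.
- **Patients already scanned:** use a reference treatment fixed by baseline prior-radiotherapy status, label the result as departure from reference, and report it separately.

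The cost is one extra field per patient, short additions to the text, and a split report for patients already scanned. It needs no further visit or procedure, no change in treatment and no change in sample size.
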